### Sample size calculation

Calculation of the sample size is based on the primary outcome variable of the study, which is high risk endometrial carcinoma. The smallest outcome group, in this case patients with high risk endometrial carcinoma, should be 10–20 times the amount of independent variables used.

Independent variables in the analyses will be: age (dichotomous), grade (1, 2 and 3) and the best predictive immunohistochemical markers. For the sample size calculation we assume to include six immunohistochemical markers in the multivariate analysis. Grade count as two variables because we use it as a trichotomous variable, which makes the total variables nine.

The amount of subjects in the smallest group therefore should lie between 90 and 180. However, as a rule of thumb, the amount of subjects should never be lower than 100.

With an expected high risk endometrial carcinoma rate of 25 % at least 400 patients with endometrial carcinoma should be included to include at least 100 patients with high risk endometrial carcinoma.

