## Abstract

**Background:**

Endometrial carcinoma is the most common gynaecologic malignancy in industrialised countries and the incidence is still rising. Primary treatment is based on preoperative risk classification and consists in most cases of hysterectomy with bilateral salpingo-oophorectomy. In patients with serous and clear cell histology a complete surgical staging is mandatory. However, in routine clinical practice final histology regularly does not correspond with the preoperative histological diagnosis. This results in both over and under treatment.

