### Comorbidity and EC

The impact of comorbidity on cancer outcome has been underestimated for a long time. Recently published data demonstrated that EC patients with cardiovascular disease, previous malignancy and diabetes have a significantly decreased survival of 15–17 % compared to patients without comorbidity [26]. Additionally, patients with diabetes and EC have more comorbidities, higher body mass index (BMI) and higher FIGO stage, compared to those without diabetes [27]. There is also a significant increase in the risk of EC-specific mortality among women with diabetes [28]. Although obesity is a risk factor for development of EC, obesity seems not related to overall survival [29]. Yet, comorbidity has demonstrated to influence the outcome in EC [30].

In summary, the main challenging issue concerning clinical management of EC patients is underscored by the discordance between the preoperative risk classification of the tumour and the final surgical pathology. At the moment a subgroup of patients needs either a secondary surgical staging procedure or additional chemotherapy and/or radiation therapy. With the current study we want to select a panel of the most accurate biomarkers that can be used in daily practice for preoperative diagnosis of EC. This will aid in improving the concordance between preoperative and final histological diagnosis and thus prevent over and under treatment. Incorporating cervical cytology and comorbidity could potentially improve a proper risk classification in EC patients.

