### Methods

Tissue specimens are collected centrally at the department of Pathology, Radboud university medical centre in Nijmegen. Pre-operative samples will be evaluated on the amount of tissue (quantitatively and qualitatively), the presence of hyperplasia, atypia, endometrial intraepithelial carcinoma (EIC), invasive growth, background endometrium, tumour percentage and tumour type and grade. IHC staining will be performed on formalin-fixed, paraffin-embedded tissue of the pre-operative samples. IHC staining will be graded semiquantitatively by considering the percentage and intensity of the staining. A staining index will be calculated as the product of staining intensity and staining area.

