### Statistical analysis

For the primary objective, results of endometrial biopsy and curettage will be compared with final pathology results. Both univariate as well as multivariate analysis will be performed to determine whether immunohistochemical markers contribute to prediction of final pathology. For the secondary objective we will also include abnormal cervical cytology and the Age-Adjusted Comorbidity-index as factors in univariate and multivariate analysis. In order to determine risk factors for recurrence Kaplan-Meier survival curves will be calculated to determine outcome after a follow-up time of 24 months. Statistical analysis will be performed using the Statistical and Data management package SPSS 20.0.

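### The declared model adjusts for age and grade but not for preoperative histological type, so it cannot fully separate a marker's added value from the biopsy diagnosis

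*Protocol article*

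**What the plan says.** The Statistical analysis section gives the purpose of the model: "multivariate analysis will be performed to determine whether immunohistochemical markers contribute to prediction of final pathology". Its covariates are named in the Sample size calculation section: "Independent variables in the analyses will be: age (dichotomous), grade (1, 2 and 3) and the best predictive immunohistochemical markers". That section then says "we assume to include six immunohistochemical markers in the multivariate analysis" and closes the count: "Grade count as two variables because we use it as a trichotomous variable, which makes the total variables nine". For the secondary objective, the Statistical analysis section adds only cervical cytology and the comorbidity index.

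Preoperative type is available. The Methods section lists, among the items to be read on each preoperative sample, "background endometrium, tumour percentage and tumour type and grade". Type also already guides surgery. The abstract states "In patients with serous and clear cell histology a complete surgical staging is mandatory", and the Primary treatment section repeats this for serous and clear cell tumours. The expected benefit of the biomarker panel is worded as a gain over the present preoperative diagnosis: "This will aid in improving the concordance between preoperative and final histological diagnosis and thus prevent over and under treatment".

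**The concern.** Whether markers improve preoperative classification is a question of added value, so the reference must be the classification that the surgeon already has. By the article's own account this consists of histological type and grade. Only grade is in the model.

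The omission matters because of how the markers were chosen. Table 1 relates every candidate except beta-catenin to histological type (IMP3, for example, is positive in 78 % of serous, 57 % of clear cell and 15 % of endometrioid tumours). Two of them, MLH1 and ARID1A, are described as separating high-grade endometrioid from serous tumours, a distinction that grade alone cannot make. The stains are made on the sample from which type is read. A marker that largely restates the morphological type can then keep an apparent independent effect and gain a place in the panel, although it tells the surgeon less than the model suggests.

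**Working it through.** **1. The plan's own figures.** Variables: 1 (age) + 2 (grade) + 6 (markers) = 9. The rule is that the smallest outcome group "should be 10–20 times the amount of independent variables used": 9 × 10 = 90 and 9 × 20 = 180. With the floor of 100 and a 25 % high-risk rate, 100 / 0.25 = 400. All figures reproduce, and they confirm that type is not counted.

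**2. Can grade stand in for type?** Table 2 (hysterectomy, unrevised) has 33 + 9 + 2 + 18 = 62 non-endometrioid tumours and 112 of grade 3. Even if all 62 were grade 3, at least 112 − 62 = 50 grade 3 tumours would be endometrioid. Grade is a partial proxy. No table of type by grade is given, and no counts of biopsy type.

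**3. Illustration for final non-endometrioid type, grade in the model.** Assumptions, per 1,000 patients:
- 120 biopsies non-endometrioid, all graded 3; 120 endometrioid grade 3; 760 grade 1 or 2.
- Marker positive in 73 % of biopsy non-endometrioid and 15 % of all others. The 73 % is the IMP3 rate weighted by Table 2: (33 × 0.78 + 9 × 0.57) / 42 = 0.735. The marker carries no information beyond biopsy type, and age is unrelated to it.
- Final type non-endometrioid in 85 %, 15 %, and 5 % down to 2 % of the three groups. Overall this is 15.8 % to 13.5 %, against 62/432 = 14.4 % in Table 2.

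Grade 3 stratum:
- marker positive, final non-endometrioid: 120 × 0.85 × 0.73 + 120 × 0.15 × 0.15 = 77.16
- marker positive, final endometrioid: 120 × 0.15 × 0.73 + 120 × 0.85 × 0.15 = 28.44
- marker negative, final non-endometrioid: 120 × 0.85 × 0.27 + 120 × 0.15 × 0.85 = 42.84
- marker negative, final endometrioid: 120 × 0.15 × 0.27 + 120 × 0.85 × 0.85 = 91.56
- odds ratio = (77.16 × 91.56) / (28.44 × 42.84) = 5.8

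In grades 1 and 2 the odds ratio is 1. A logistic model with grade and one common marker effect gives 3.3 (at 5 %) to 4.2 (at 2 %). With biopsy type added it is 1.0 by construction.

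**4. Same marker, high-risk outcome.** The plan's primary outcome is high-risk carcinoma at 25 %, which the article does not define. Assumed rates are 90–95 % for biopsy non-endometrioid, 65–85 % for endometrioid grade 3 and 5–10 % for grades 1 and 2 (overall 22 % to 29 %). The logistic model with grade gives a marker odds ratio from 1.1 (90 %, 85 %, 10 %) to 2.0 (95 %, 65 %, 5 %). If both grade 3 groups have the same rate, it is 1.0.

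**5. Room for type.** Expected high-risk patients among those enrolled: 432 × 0.25 = 108.

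| Parameters for type | Variables | High-risk patients, 10 to 20 per variable | N at 10 per variable | Per variable with 108 |
|---|---|---|---|---|
| 1 | 10 | 100–200 | 400 | 10.8 |
| 2 | 11 | 110–220 | 440 | 9.8 |
| 3 | 12 | 120–240 | 480 | 9.0 |

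**The case against.** The strongest reply is that grade is already in the model. The Discussion describes the study's focus as type and grade together, so half of the baseline is present. This stands, and it limits the size of the problem. A reader might leave grade out and infer an odds ratio of about 6.5 for an uninformative marker, against 1.0 once type is added. That figure belongs to a model containing the marker alone, for final non-endometrioid type. The plan's model includes grade, and its declared outcome is high risk at 25 %, which cannot be non-endometrioid type alone (14.4 %). The documents therefore do not support the claim that an uninformative marker would look like a strong predictor of the declared outcome, or that any reported improvement would be unreal.

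A second reply is that the list sits in the sample size section of a condensed article, that six markers is an assumption, and that biopsy results are compared with final pathology anyway. The wording nevertheless commits the analyses to those variables, the count closes the list, and nothing elsewhere contradicts it. The comparison with final pathology does not adjust marker effects for type. The formal test and the measure of performance may well be set out in a fuller plan, and their absence here is not the point.

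A third reply is that type may cost more than one parameter, since 13 % of preoperative samples showed atypical hyperplasia (about 0.13 × 432 = 56 if the base is patients). This stands, and the fix has to place these samples.

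**Conclusion.** The point holds. The declared covariates leave out a variable that is recorded, already guides surgery and is closely tied to the markers, so the model cannot fully distinguish added value from the biopsy diagnosis. The bias is partial. Its true size cannot be computed, because the article gives no biopsy type counts, no cross-table of type and grade, and no definition of high risk.

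Under the assumptions shown, the spurious odds ratio is about 3.3 to 4.2 for final type, which is one part of the primary objective, and about 1.1 to 2.0 for a high-risk outcome near 25 %. A marker with real information beyond type would keep part of its effect. All of this assumes that grade means biopsy grade, which the sample size section does not say.

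**What to change.** Define the baseline model as age, reviewed preoperative grade (stated to be biopsy grade) and reviewed preoperative type in two levels: non-endometrioid against all other, with atypical hyperplasia in the latter. State also how atypical hyperplasia is coded for grade, without a further level. Judge the markers by what they add to this baseline, for example with a joint likelihood-ratio test and the change in optimism-corrected AUC.

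Restate the count as ten variables and 100 to 200 high-risk patients. The floor of 100 and N = 400 then still meet the plan's lower bound, with about 108 high-risk patients expected. Keep a biopsy-versus-curettage term out of the main model: it would make 11 variables and require 110 against those 108.

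The cost is one more parameter and a change of wording; no new data are needed. Some markers will look less impressive. Since the Discussion says that analysis is under way, the baseline should be fixed before the panel is chosen.

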## Discussion

A total of 432 EC patients from nine hospitals were collected between September 2011 and December 2013. The inclusion of patients has finished and we are now analysing the data. Follow-up will be completed in December 2015. The various histological subtypes of EC are all represented in this study group with 86 % EEC, 8 % UPSC and 2 % CCC based on hysterectomy evaluation. This is in line with percentages reported in the Netherlands Cancer Registry [32]. Clinicopathological characteristics are shown in Table 2. Atypical hyperplasia is diagnosed in 13 % of the preoperative endometrial samples, where final diagnosis on hysterectomy was EC.

**Table 2 Tab2:** Clinicopathological characteristics of 432 women with endometrial carcinoma. Values are presented as median (range) or number (%)

Characteristics		
Age at primary surgery, years	66	(41–90)
Pre-operative histology^a^		
Office endometrial biopsy	311	(72.0)
Hysteroscopic biopsy	128	(29.6)
Curettage	75	(17.4)
Histological subtype^b^		
Endometrioid	370	(85.6)
Serous papillary	33	(7.6)
Clear cell	9	(2.1)
Mucinous adenocarcinoma	2	(0.5)
Carcinosarcoma	18	(4.2)
Histological grade^b^		
1	193	(44.7)
2	127	(29.4)
3	112	(25.9)
FIGO 2009 stage		
I	362	(83.8)
II	27	(6.3)
III	35	(8.1)
IV	8	(1.9)

^a^ 82 patients have more than one pre-operative histological sample

^b^ Unrevised classification based on hysterectomy specimen

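### Age is fixed as a two-category predictor although it is held in years; a linear term costs the same one degree of freedom, so entering age in years is a free, modest improvement

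*Protocol article*

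**What the plan says.** The Sample size calculation section states the form of the multivariable model. The independent variables are "age (dichotomous), grade (1, 2 and 3) and the best predictive immunohistochemical markers". For planning, "we assume to include six immunohistochemical markers in the multivariate analysis". On the count, it adds "Grade count as two variables because we use it as a trichotomous variable", "which makes the total variables nine".

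The smallest outcome group "should be 10–20 times the amount of independent variables used", with the further rule that "the amount of subjects should never be lower than 100". At the expected high-risk rate of 25 % this gives at least 400 patients.

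Table 2 in the Discussion reports "Age at primary surgery, years" as median 66, range 41–90, for the 432 enrolled women. The Statistical analysis section gives no other form for age, and no reason for the split appears anywhere in the article.

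**The concern.** Splitting age treats all women on one side of the cut as having the same risk and puts the whole age effect into one step at the cut. If risk changes gradually with age, the split variable describes it less well than age in years.

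The usual reason for grouping a predictor in a plan built on patients per variable is to save degrees of freedom. Here nothing is saved, because a straight-line term in years also counts as one variable.

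Two things are at stake. The model predicts somewhat less accurately. And the part of the age effect that the split misses can be picked up by any other predictor that varies with age. The study wants to know what the markers add, and secondarily what cervical cytology and comorbidity add, so leftover age effect can make such a predictor look more useful than it is.

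**Working it through.** **1. The plan's own figure.** Inputs are from the Sample size calculation section.
- Variables: 1 (age) + 2 (grade) + 6 (markers) = 9.
- High-risk patients: 10 × 9 = 90 to 20 × 9 = 180; with the floor, max(90, 100) = 100.
- Total: 100 / 0.25 = 400. The stated figure reproduces.

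**2. The same count with age in years.** A linear term is one variable: 1 + 2 + 6 = 9. The range stays 90–180 and the total stays 400.

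**3. Information kept on the age term.** For a linear effect, the share kept by a split at c is the squared correlation between x and the indicator x > c. For normal x this is φ(c)² / [p(1 − p)], where p is the share on one side. For uniform x it is 3p(1 − p).

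| Age distribution (assumed) | Split | Kept | Lost |
|---|---|---|---|
| Normal | 50/50 | 2/π = 0.637 | 36 % |
| Normal | 40/60 | 0.622 | 38 % |
| Normal | 30/70 | 0.576 | 42 % |
| Normal | 25/75 | 0.539 | 46 % |
| Normal | 20/80 | 0.490 | 51 % |
| Uniform | 50/50 | 3 × 0.25 = 0.75 | 25 % |

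Table 2 gives a median and range but no standard deviation. With a normal distribution centred at 66, truncated to 41–90, and an assumed SD of 8 to 11 years, the loss is 34–36 % for a cut at 65 or 66, 37–42 % at 70 and 41–48 % at 60. A logistic simulation with 432 patients, 25 % events and a median split gave an information ratio of 0.64, in agreement with 2/π.

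For the age term alone, 432 patients under a median split carry the information of 432 × 0.637 = 275.

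**4. What reaches the other predictors.** The article gives no age effect and no marker–age correlation, so these simulations are illustrations. All assume an age SD of 10 years, a median split, and an odds ratio of 1.03 to 1.05 per year.
- *Weakly age-related marker* (25 % positive, true odds ratio about 3, correlation with age 0.2–0.3, event rate about 18–19 %): splitting age raises the marker's log odds ratio by about 0.03–0.07, against a standard error of about 0.27. The area under the ROC curve falls by 0.013–0.023.
- *Predictor with no true effect* (432 patients, about 25 % events): the false-positive rate at correlations of 0.3, 0.5 and 0.7 is about 5 %, 8 % and 12 % at 1.03 per year, and about 8 %, 13 % and 24 % at 1.05. With age in years it stays at 4–6 %.

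**5. Room for a non-linearity check, by the plan's minimum of 10 per variable.**
- One extra degree of freedom: 10 variables, 100 high-risk patients, 100 / 0.25 = 400. This fits.
- Two extra: 11 variables, 110 high-risk patients, 110 / 0.25 = 440. This exceeds both the planned 400 and the enrolled 432.

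**The case against.** The best defence is that age is a background covariate. No objective tests an age effect, so information lost on that term is not information lost on the study's question. This stands. It is why power to detect an age effect is not a fair measure of the harm, and why the shift in a weakly age-related marker is only about 0.1–0.3 of its standard error.

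In the secondary models the Age-Adjusted Comorbidity-index, by its name, already carries some age, so the binary term is not the only route by which age enters. That also stands. But it makes the index a predictor likely to be correlated with age, and so one that could absorb what the split leaves behind.

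Stronger readings that a reader might infer are not supported:
- *The sample size is wrong, or a third of the study is wasted.* The total of 400 reproduces and does not change with the fix. The loss concerns one of nine variables.
- *The cut-point will be picked from the data.* The article names none, but a fuller protocol or analysis plan, not shown, may do so. Only the decision to split is fixed here.
- *The staining index will be dichotomised too.* The Methods subsection defines it as a product of intensity and area and does not say how it enters the model.

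**Conclusion.** The point holds as a modest one. The article fixes a two-category age variable, holds age in years, gives no reason for the split, and saves no degree of freedom by it.

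The loss on the age term is about 36 % for normal age cut at the median, about 25 % for uniform age, and up to about 50 % for an off-centre cut. All of these assume an effect roughly linear on the log-odds scale. If risk truly stepped up at one age, the comparison would be less favourable to the linear term.

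The effect on the study's question is a slightly less accurate model and a leftover age effect in predictors correlated with age. It is probably small for weakly correlated markers and could matter for strongly age-related predictors. Neither the sample size nor the patients-per-variable argument is affected.

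**What to change.** In the Sample size calculation section, replace the dichotomous form of age with *age (continuous, in years)* and use that form in the prediction models. Keep age groups for descriptive tables only.

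If non-linearity is checked in the main model, limit it to one extra degree of freedom. Otherwise run it as a sensitivity analysis.

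The change needs no new data or patients. The linear term leaves the nine variables and the total of 400 as they are, and the one-degree-of-freedom check still fits 400 at the plan's lower bound. The article reports that analysis is under way, so the change should be made and recorded before the models are final.

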### Tissue specimens

The endometrial biopsy or curettage on which the diagnosis of EC was made will be used for systematic evaluation by pathologists with special interest in gynaecologic pathology. Additional IHC analysis of IMP3, p53, ER, PR, MLH1, PTEN, beta-catenin, p16, Ki-67, stathmin, ARID1A and L1CAM will be performed (Table 1). Final pathology will be reviewed by the expert pathologists and compared with the preoperative histological diagnosis. The pathologists will be blinded for clinicopathological information and outcome.

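### The events-per-variable count behind the 400 patients covers the six markers to be retained, not the twelve to be screened; on all 15 candidate parameters it is about 7 rather than 11

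*Protocol article*

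**What the plan says.** The section Sample size calculation names the outcome that drives the size: "Calculation of the sample size is based on the primary outcome variable of the study, which is high risk endometrial carcinoma". Its rule is that the smaller outcome group "should be 10–20 times the amount of independent variables used".

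The variables are listed as "age (dichotomous), grade (1, 2 and 3) and the best predictive immunohistochemical markers". On the markers it states: "For the sample size calculation we assume to include six immunohistochemical markers in the multivariate analysis". It then totals the variables: "Grade count as two variables because we use it as a trichotomous variable, which makes the total variables nine". From nine variables it derives 90 to 180 high-risk patients, sets 100 as an absolute minimum, and reaches 400 patients at an expected high-risk rate of 25 %.

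The section Tissue specimens lists the markers to be stained: "Additional IHC analysis of IMP3, p53, ER, PR, MLH1, PTEN, beta-catenin, p16, Ki-67, stathmin, ARID1A and L1CAM will be performed". With ER and PR counted separately, that is twelve. The Abstract and the closing summary of Comorbidity and EC both say that the panel is to be selected in this study. The section Statistical analysis gives the method: "Both univariate as well as multivariate analysis will be performed to determine whether immunohistochemical markers contribute to prediction of final pathology".

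**The concern.** An events-per-variable rule is meant to limit overfitting. Overfitting comes from every predictor that had a chance to enter the model, not only from those left at the end. If only the survivors are counted, screening costs nothing: keeping six of twelve and keeping six of a hundred would need the same number of patients. The article names no six markers and gives no reason for six, while the wording on the best predictors and the aim of selecting a panel point to a choice made on these patients. Half of the markers examined against the outcome are therefore left out of the count that justifies 400 patients.

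Selecting the panel is the purpose of the study, and the panel is meant to inform who needs more extensive surgery. If its performance is read straight from the data that chose it, the discrimination reported will be too high and the predicted risks too extreme, with nothing in the stated sample size to warn the reader.

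**Working it through.** **Inputs.** From Sample size calculation: age 1, grade 2, six markers counted, multiplier 10 to 20, minimum 100, high-risk rate 25 %. From Tissue specimens: twelve markers. From the Discussion: 432 patients enrolled. Assumption: one parameter per marker, in line with the single staining index described under Methods.

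**1. The plan's own figure**
- Variables: 1 + 2 + 6 = 9
- High-risk patients: 9 × 10 = 90 to 9 × 20 = 180
- Larger of 90 and 100: 100
- Patients: 100 / 0.25 = 400

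The stated 400 is reproduced exactly. On this count, 100/9 = 11.1 per variable, and with 432 × 0.25 = 108 high-risk patients, 108/9 = 12.0.

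**2. The same rule on all candidates**
- Parameters: 1 + 2 + 12 = 15
- High-risk patients: 15 × 10 = 150 to 15 × 20 = 300
- Patients at 25 %: 150/0.25 = 600 to 300/0.25 = 1200
- Available per candidate: 100/15 = 6.7 as planned; 108/15 = 7.2 as expected from 432

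Read the other way, 100 to 108 high-risk patients at 10 each support 10 parameters, that is 10 − 3 = 7 candidate markers beside age and grade.

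**3. What the selection does to apparent performance**

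Simulated logistic models: n = 432, 25 % events, 400 runs, each evaluated on 20,000 new patients. Age and grade were predictive, and the twelve markers were independent and continuous. The selected six were those with the strongest univariate association. Two settings were run: no marker predictive, and three predictive (log odds ratio 0.4 per SD). In the second, the prespecified six included all three real markers. Optimism is the apparent AUC minus the AUC in new patients.

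| Setting | Panel | Apparent AUC | AUC in new patients | Optimism | Calibration slope |
|---|---|---|---|---|---|
| Three real markers | six prespecified | 0.769 | 0.739 | 0.030 | 0.86 |
| Three real markers | best six of twelve | 0.774 | 0.734 | 0.040 | 0.82 |
| Three real markers | all twelve | 0.778 | 0.731 | 0.047 | 0.78 |
| No real marker | six prespecified | 0.726 | 0.689 | 0.037 | 0.84 |
| No real marker | best six of twelve | 0.736 | 0.682 | 0.054 | 0.77 |
| No real marker | all twelve | 0.740 | 0.680 | 0.060 | 0.73 |

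The best six of twelve lies closer to fitting all twelve than to fitting six fixed in advance. Selection itself adds 0.040 − 0.030 = 0.010 to 0.054 − 0.037 = 0.017 to the AUC optimism.

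**The case against.** **The plan meets its own rule.** This is right. The rule refers to the variables used in the model, the section lists nine, and 11.1 per variable exceeds 10. A reader might infer that the study misses its own floor or that the arithmetic is wrong. Neither is so. Counting candidates is a sounder standard, but it is not the one the article states.

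**The secondary factors.** The section Statistical analysis adds that for the secondary objective "we will also include abnormal cervical cytology and the Age-Adjusted Comorbidity-index as factors in univariate and multivariate analysis". A reader might infer that these two should be counted as well. But the calculation is expressly for the primary outcome, and leaving a secondary analysis out of it is no error.

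**The number of high-risk patients is unknown.** The article does not define high risk. Table 2 shows 112 grade 3 tumours, but that grading is unrevised and only a possible proxy. For that reason the count above uses 100 and 108. Taking 112 would give 112/15 = 7.5, still below 10.

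**The selection rule is not spelled out.** True. Univariate ranking in the simulation is an assumption. That the choice is made on the data is not: the calculation refers to the best predictors and the aim is to select a panel.

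**Validation may be planned elsewhere.** Also true. A full protocol or SAP could provide shrinkage or internal validation, and its absence from the article is not the charge. The charge concerns the variable count, which the article does state.

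**The setting without any real marker is too harsh.** Fair. Table 1 cites an earlier association for every marker, so that setting is an extreme. False-positive rates computed under it should not be read as a forecast for this study.

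**Conclusion.** The point holds as a methodological weakness in the stated basis for the sample size. The calculation counts the six markers retained, whereas a panel selected from the data calls for counting the twelve screened. On 15 candidate parameters there are 6.7 (100 high-risk patients) to 7.2 (108) per parameter, against the 10 that the plan takes as its minimum. Reaching 10 would take 150 high-risk patients, about 600 in all at 25 %.

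The consequence is moderate. Apparent AUC would be too high by about 0.04 to 0.05 if reported uncorrected, of which 0.01 to 0.02 is due to the selection. These figures depend on the assumed effects, on independent markers and on the assumed selection rule. The counts depend only on one parameter per marker and the 25 % rate; a marker entered in several categories would lower them further. A reader might infer that the cohort is too small to use or that the panel is bound to be reported too favourably. The documents support neither: the optimism can be estimated and corrected with the 432 patients at hand.

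**What to change.** - In Sample size calculation, state that twelve markers are candidates, that with age and grade this makes 15 parameters, and that the cohort provides about 7 high-risk patients per candidate parameter. No further enrolment is needed.
- Keep the aim of selecting a panel. Enter all twelve markers as candidates and choose among them by a procedure written down in advance, preferably penalised estimation.
- Report AUC and calibration corrected for optimism, from a bootstrap that repeats the whole marker selection in every resample. A bootstrap of the final six alone would miss the part due to selection.

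The Discussion says enrolment is closed and analysis has begun, so this should be settled before the panel is chosen.

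The cost is a change of wording and modest extra analysis, possibly outside SPSS 20. The stated events per variable and the reported AUC will look slightly less favourable.
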